**Figure 1 F1:**
[figure not shown]
Magnet4Europe timeline. †Activity for group 1; ‡Activity for group 2; *Activity for both groups.

The intervention consists of five distinct components: The Magnet blueprint, one-to-one twinning between European hospitals and US Magnet designated hospitals, learning collaboratives involving group meetings to share best practices, critical mass and communication and feedback.

The first part of the intervention comprises the elements outlined in the Magnet manual of organisational redesign. This contains a step-by-step blueprint through the five overarching Magnet components: (1) structural empowerment of clinical staff, (2) transformational leadership, (3) exemplary and evidence-based professional practice, (4) new knowledge, innovations and improvements and (5) empirical outcomes. These principles serve as continuous feedback loops as to whether organisational changes are producing the intended outcomes for health professionals and patients. The manual provides definitions of the principles and gives examples of evidence-based indicators that reflect progress towards achieving them. Using the Magnet4Europe Gap Analysis Tool (adapted from the ANCC Magnet Gap Analysis tool), each participating European hospital will, in collaboration with their Magnet twinning partner, perform a gap analysis that will illuminate the gap between the as-is situation and the aspirational organisational features as delineated in the Magnet blueprint. The tool should be used for initial and continuous assessment of workplace redesign. This will increase the ability of hospitals to identify and prioritise learning and infrastructure needs, while also identifying initiative-wide gaps and exemplars for systematic improvement and recognition. Drawing on the results of the gap analysis, each hospital will be responsible for tailoring and individualising the interventions to their hospital-specific context and developing a concrete, written action plan that will be monitored and executed during the course of the intervention period. Results of the gap analysis and the effect of tailored interventions will serve as feedback to enhance learning.

The second intervention component consists of one-to-one twinning between European hospitals aspiring to implement the Magnet model and longstanding US Magnet designated hospitals. This seeks to promote capacity building through transfer of knowledge, skills, tools, technologies and best practices, thereby supporting positive reciprocal organisational changes.^55^ An equal number of US Magnet hospitals—recognised for having an excellent work environment—will be recruited; allowing for a 1:1 twinning ratio of European intervention hospitals with US Magnet Hospitals. The twinning pairs will meet every two weeks virtually and two face-to-face mentoring sessions are planned each year when travel is safe. Face-to-face meetings between both parties allow for a profound, impact- and meaningful experience that maximises the effect of the capacity building activities facilitating the intended organizational redesign.

Third, learning collaboratives will take place throughout the duration of the project and will be accessed and attended by all European hospitals in which the intervention is taking place at that point in time. The learning collaboratives will also involve policymakers, so as to promote sustainability. Learning collaboratives build on the concept of communities of practice,^56^ involving people coming together to engage in a process of learning in a shared domain of interest. These will be held monthly using remote means of communication with the possibility of in-person meetings annually when travel is safe. Effective elements of collaboratives, that is, learning sessions, action periods and a collaborative extranet, will be implemented.^57–59^

Fourth is the creation of a critical mass of participating hospitals promoting innovation, attracting public interest, engaging stakeholders and fostering replication and scaling of the intervention. Achieving a critical mass is essential for sustainability and scale-up of the intervention.^60^ Critical mass shifts the context from one in which the change activities are unusual to one in which they are the norm. This long-standing principle in organisational sociology suggests that organisations become more open to and actively seek out change as the intervention gains legitimacy among peer institutions; this is particularly true in complex workplaces such as those found in healthcare.^61 62^ Critical mass also maximises the network exchanges and opportunities for feedback that arise out of other elements of our intervention such as the learning collaborative. This is supported by recent experience with the Magnet model.^63 64^

A fifth component of the intervention is to provide regular survey feedback to hospitals on clinicians’ reports on work conditions and well-being on the hospital level, separately for physicians and nurses.^65^ Hospitals will be anonymised using a randomly generated letter code allowing each hospital to identify themselves but not any of the other hospitals. Data will only be reported in aggregated form and will not highlight a single individual’s data.

### Evaluation of the effect of the intervention

A mixed-methods evaluation will be conducted to examine the effect of the intervention, including quantitative and qualitative components.

The guiding framework for our quantitative evaluation is the Quality Health Outcomes Model—as adapted by Aiken and colleagues^66^—based on a conceptual framework that sets out mechanisms relating organisational attributes to clinician and patient outcomes. Their model is theoretically founded on Donabedian’s early conception of associations between structures, processes and outcomes^67^ including the dynamism between model components that was proposed in the Health Quality Outcomes Model.^68^ The Job Demands-Resources model also informed the choice of survey items, seeking to understand the intervention’s impact on the imbalance between demands on the clinician and the resources available to clinicians to deal with these demands.^69^ Job demands refer to aspects of the job that require sustained physical or mental effort and are associated with certain physiological and psychological costs. Job resources describe aspects of the job that are related to achieving work goals, reducing job demands and the associated physiological and psychological costs and stimulating personal growth and development.

The qualitative part of the study aims first, to evaluate the implementation process, adaptation, reach and quality as well as mechanisms of impact manifested in participants’ responses, mediators, unexpected pathways and consequences; and second, to explore barriers and enablers of the implementation and the experiences of the change process from the perspectives of health professionals and persons involved in leading the implementation.^70^

### Quantitative evaluation

#### Quantitative data collection

Quantitative data collection across countries is standardised using an online data collection platform. Quantitative survey data will be collected at three points in time, that is, at baseline (T0) in months 11–12 of the project timeline, at T1 (months 28–29) and T2 (months 41–42) (figure 1) during an 8 week period. An open cohort design will be employed in which all eligible nurses and physicians are invited to participate in each of these three measurement points (T0–T2). Nurses and physicians will be recruited within each hospital at baseline and will be asked to participate in surveys with repeated measures taken over the three points in time allowing partially longitudinal follow-up of a cohort of individuals. Initial non-participants and new employees will be invited to join the study at later measurement points. Regular reminders will be sent to any clinicians (registered on the platform) through the online data collection platform who have not or only partially completed the survey. Individual informed consent for participation will be obtained by the researchers at the first contact (online supplemental file 2). Each record of informed consent is retained on the online platform.

10.1136/bmjopen-2021-059159.supp2Supplementary data

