### Randomisation

Randomisation to intervention and control group is at the hospital level. Within each country, hospitals will be matched on three characteristics, (1) bed size, (2) teaching status and (3) high technology, using a Euclidian distance matrix based on the smallest within pair covariate distance. Subsequently, simple random sampling—allowing for selection with equal probability—will be used to allocate one hospital within each matched pair of hospitals to the immediate intervention group or the wait list control group. Both immediate intervention group and wait list controls will be informed which group they have been allocated to. Given the characteristics of the intervention in which active participation of the hospitals is required, blinding to the intervention will not be possible.

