### Intervention

A multicomponent intervention comprising organisational redesign of hospitals will be implemented in both arms of the study. The intervention was launched in the immediate intervention group in month 10 of the project (October 2020) and will have a total duration of 31 months. The intervention in the usual-practice wait list control group will be initiated in month 17 (May 2021) and will last for 24 months (figure 1).

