#### Data analysis

Regression models to estimate the association between the intervention and outcomes will include fixed effects of time, intervention and intervention by time. Hospitals represent higher order units of analysis, and clinicians the lower order unit of analysis. Countries will be treated as fixed effects. Repeated measures on nurses and physicians will also be appropriately modelled. More complex multilevel structural models will be employed to examine indirect and moderated associations between the process measures which we would expect to respond to the intervention and our outcome measures. All analyses will be conducted according to intention-to-treat. Data on hospital characteristics (eg, size, teaching status) and clinicians (eg, gender, age) will be collected and used to adjust for potential confounders in the regression analyses. Statistical significance will be assessed at the 5% level. Occasional missing data will be limited by the electronic survey implementation using a force response option for each item. Data analysis will be conducted using SAS software, V.9.4 (and subsequent releases) of the SAS system for windows (SAS Institute, Cary, North Carolina).

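### The survey called baseline (T0, months 11–12) follows the month-10 launch in the immediate arm, so an estimate of change from T0 may subtract an arm difference that has already arisen, of unknown size

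*Protocol article*

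**What the plan says.** All references are to the protocol article.

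- **Intervention**, immediate arm: "The intervention was launched in the immediate intervention group in month 10 of the project (October 2020"; it "will have a total duration of 31 months".
- **Intervention**, wait list: "The intervention in the usual-practice wait list control group will be initiated in month 17 (May 2021) and will last for 24 months".
- **Quantitative data collection**: the first survey is taken "at baseline (T0) in months 11–12 of the project timeline", and the later ones "at T1 (months 28–29) and T2 (months 41–42". The same section says "Nurses and physicians will be recruited within each hospital at baseline", and individual consent is taken at first contact.
- **Randomisation**: "Both immediate intervention group and wait list controls will be informed which group they have been allocated to". No date is given. This section and Limitations both say that hospitals could not be blinded.
- **Data analysis**: the regression models "will include fixed effects of time, intervention and intervention by time". The section does not name the primary contrast, and does not say whether the intervention term means arm or time-varying exposure.

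Limitations discusses contamination, slow uptake and the lack of a transition period. Neither it nor any other section mentions that the first survey follows launch in one arm.

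**The concern.** A baseline should precede both the intervention and knowledge of allocation. Here T0 does so in neither respect for the immediate arm. In a model with time, arm and arm-by-time terms, and T0 as the first occasion, the interaction compares the arms on change from T0. Whatever already separates the arms at T0 then enters the reference level and is removed from the estimate.

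Three things could separate them:

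- an early effect of the intervention, which if beneficial would make the estimate too small;
- a reaction to being in the immediate or the wait-list group, on a self-reported burnout scale, which could act in either direction;
- a different mix of respondents, because recruitment takes place after launch in one arm.

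The second and third do not depend on the intervention having taken hold. A T0 difference therefore cannot simply be treated as chance imbalance to be adjusted away. T0 is also the only survey at which the wait list is unexposed, yet it serves as the reference and not as a comparison.

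**Working it through.** **1. Calendar.** If month 10 is October 2020, month 17 is May 2021, as the protocol states. The programmes end after months 10 + 31 − 1 = 40 and 17 + 24 − 1 = 40, so the numbering is consistent and a slip in month numbers is unlikely. T0 falls in November–December 2020.

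**2. The protocol's own sample size.** For 30% against 24%, two-sided 5% and 80% power, the requirement is 859 per arm, or 1,718. The design effect is 1 + (200 − 1) × 0.025 = 5.975, and 1,718 × 5.975 = 10,265, against the stated 10,253. The figure reproduces and this point does not affect it. It supplies only the 6-point scale used in step 5.

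**3. Months of exposure at each survey** (launch on the first day of the stated month, capped at the planned durations):

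| Survey | Immediate | Wait list | Difference |
|---|---|---|---|
| T0 (months 11–12) | 1–3 | 0 | 1–3 |
| T1 (months 28–29) | 18–20 | 11–13 | 7 |
| T2 (months 41–42) | 31 | 24 | 7 |

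Only the month of launch is given. If both arms started at the end of their month, exposure at T0 would be 0–2 months and the 7-month difference would stand.

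**4. Share of the follow-up contrast that is subtracted.** Let f(t) be the effect after t months. Change from T0 estimates [f(immediate) − f(wait list)] at follow-up minus f(exposure at T0). The share lost is f(exposure at T0) divided by the follow-up contrast. The protocol gives no f, so each shape below is an assumption.

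| Assumed build-up | Share lost |
|---|---|
| Linear, launch on the first of the month | 1/7 = 14% to 3/7 = 43% |
| Linear, launch at month end | 0/7 = 0% to 2/7 = 29% |
| Quadratic, at T1 | 1/(18² − 11²) = 1/203 = 0.5% to 9/(20² − 13²) = 9/231 = 3.9% |
| Quadratic, at T2 | 1/(31² − 24²) = 1/385 = 0.3% to 9/385 = 2.3% |
| 3-month lag, then linear | 0% |

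The 43% needs every response to come at the very end of the T0 window.

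**5. The linear case in points.** If 6 points accrue evenly over 31 months, the rate is 6/31 = 0.194 points per month. A 7-month difference is worth 1.35 points. Change from T0 recovers 6 × 0.194 = 1.16 down to 4 × 0.194 = 0.77.

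**6. A different denominator.** As a share of the full 31-month effect, the linear case subtracts 1/31 = 3% to 3/31 = 10%. This is compatible with 14–43%, which is a share of the smaller contrast that the design can observe.

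**7. Faster build-up.** If the effect grew linearly and levelled off at 18 months, the contrast in mid-T1 (19 against 12 months) would be 1 − 12/18 = 0.333, and the effect at the end of T0 would be 3/18 = 0.167, a share of 50%. So 43% is the top of the linear range in step 4 and not a mathematical ceiling.

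**The case against.** The strongest reply is that little can have happened by T0. Limitations expects the intervention to be slow to take hold, and allows that its effect may show only after the study ends. The first steps are a gap analysis and a written action plan. The survey-feedback component cannot precede the first survey. Under slow-onset shapes the loss is 0–4%. This stands as regards an early effect, but it does not answer reaction to allocation or selective response.

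A second reply is that Data analysis does not define the effect as change from T0. The same terms also yield the arm difference at T1, and the choice of contrast may sit in an analysis plan that is not shown. This stands too: change from T0 is the natural reading, not a stated fact. The dates, however, are fixed in the protocol itself.

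A third is that knowledge of allocation is documented for hospitals, not for individual clinicians, and without a date. The immediate arm must have known by month 10. For the wait list it is a strong inference: Limitations says that the blueprint and the twin's name were withheld from those hospitals before their start, which implies that they knew their status.

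A reader might infer that the effect will be cut by 14–43%, or that a modest reaction to allocation would remove most of it. The document does not support either. The first rests on linear build-up from 1 October, which fits Limitations poorly, and no source gives a size for the second. Much of the apparent severity also comes from the 7-month denominator, which arises because the wait list starts in month 17. That is a separate and larger dilution.

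**Conclusion.** The point holds as a defect in how T0 is described and used. T0 is not a pre-intervention measure in the immediate arm, and nothing in the protocol acknowledges or handles this. Any arm difference present at T0 is subtracted if the effect is read as change from T0.

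The size cannot be determined. As a share of the 7-month contrast it runs from near 0% under lagged or slow onset to about 43% under linear build-up with the earliest launch and the latest responses. A faster, levelling build-up would give more, but nothing in the protocol suggests one. An early benefit biases towards underestimation, while a reaction to allocation or selective response could act either way.

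A reader might also conclude that T0 must leave the primary model, or that months since launch should become its exposure variable. Neither follows. Exposure coding builds an assumed shape into the main result, and it does not remove reaction or selection bias. Omitting T0 gives up adjustment for hospital differences in burnout with only about 51 to 60 clusters.

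**What to change.** 1. Reconcile the launch month in Intervention with the T0 window in Quantitative data collection. If both dates stand, describe T0 as an early post-launch measurement and not as an unexposed baseline.
2. Keep the planned model, but state which contrast is primary and that change from T0 may be biased.
3. Prespecify a companion estimate: the arm difference at T1, adjusted only for variables fixed before launch (matched pair, or bed size, teaching status and technology; and country).
4. Report the arm difference at T0 and the T0 response by arm.
5. Optionally, add a sensitivity analysis that codes actual months since launch at T0, over more than one build-up shape.

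The cost is wording and one or two extra models, with no new data. The companion estimate will be less precise than one that uses T0. It does not cure the wait list's own exposure at T1, or selective response at T1. Its value is that it does not depend on the T0 outcome.

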#### Quantitative measures

The main survey for nurses and physicians contains a core set of outcomes and main explanatory and process variables directly linked to the Magnet4Europe Magnet Gap Analysis Tool. All study measures are based on validated instruments.

All survey items will be translated in Dutch, English, German, Norwegian and Swedish. When available, validated translations of instruments will be used. If no validated translation is available, a prespecified translation procedure will be applied. First, a forward translation will be performed by a researcher involved in this research; the language in which the item is translated is the native language of the researcher. Second, other researchers within the country research group will thoroughly assess the forward translation in multiple phases until consensus is reached on each item.

#### Primary outcome

Burnout is the primary outcome measure and will be measured on individual level using the 9-item EE subscale of the MBI.^53^ In addition, the Burnout Assessment Tool (BAT), a 12-item novel self-report questionnaire will also be used to measure burnout.^71–73^ The combination of both instruments to assess burnout, allows for: (1) a direct comparison of levels of EE with previous studies in the medical field (using the EE-subscale of MBI) and (2) an up-to-date assessment of the more comprehensive burnout syndrome as well as a reliable estimation of the number of respondents with severe burnout symptoms and a comparison with the level of burnout of the national workforce.

#### Covariates

Secondary outcome measures include work engagement (UWES-3),^74^ job satisfaction,^75 76^ depression (PHQ-2),^77^ anxiety (GAD-2),^78^ general health (SF-8),^79^ sleep quality (PSQ),^80^ intent to leave the hospital,^75 76^ absenteeism and presenteeism (HPQ),^14^ workability, work-life conflict, team commitment, organisational commitment,^81^ and whether clinicians would recommend the hospital.

Core exploratory variables include work environment (PES-NWI),^82^ various measures of staffing and workload (NPQS),^83^ care left undone,^84^ operational failures, emotional demands (SIMPH),^85^ red tape,^86^ role conflicts (NPQS), job control, skill use, value congruence, performance feedback, opportunities for learning and development^87^ and intrinsic motivation (WEIMS).^88^

Supplementary survey items are used to test more specific hypotheses.^69 89^ These items contain measures on qualitative job insecurity,^90^ emotional dissonance,^91^ task variety (QEEW),^92^ role clarity (NQPS),^83^ basic need satisfaction^93^ and engaging leadership.^94^

Productivity measures consist of staff turnover rate, sickness absence rate, number of vacancies and the use of agency staff—measured at organisation level—complemented by previously mentioned secondary outcome measures, for example, absenteeism and presenteeism are measured at individual level by means of a survey. Productivity measures evaluated at the level of the organisation are evaluated over the period of 1 calendar year. The timeframe to evaluate absenteeism on individual level is 28 days, ie, participants are asked to indicate the number of scheduled work days they have missed during the past 28 days. The timeframe to evaluate presenteeism on individual level is 1 year.

#### Data analysis

Regression models to estimate the association between the intervention and outcomes will include fixed effects of time, intervention and intervention by time. Hospitals represent higher order units of analysis, and clinicians the lower order unit of analysis. Countries will be treated as fixed effects. Repeated measures on nurses and physicians will also be appropriately modelled. More complex multilevel structural models will be employed to examine indirect and moderated associations between the process measures which we would expect to respond to the intervention and our outcome measures. All analyses will be conducted according to intention-to-treat. Data on hospital characteristics (eg, size, teaching status) and clinicians (eg, gender, age) will be collected and used to adjust for potential confounders in the regression analyses. Statistical significance will be assessed at the 5% level. Occasional missing data will be limited by the electronic survey implementation using a force response option for each item. Data analysis will be conducted using SAS software, V.9.4 (and subsequent releases) of the SAS system for windows (SAS Institute, Cary, North Carolina).

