## Discussion

This paper describes the theoretical framework, conceptual design and methodological approaches of the EU H2020 Magnet4Europe project, which aims to evaluate the transfer, implementation, scale up and cost-effectiveness of the Magnet model of organisational redesign in a European context as a system-level approach to improve clinician well-being. Mental health and well-being is among one of the highest priorities of the public health agenda in the EU.^1^ This is based on the growing awareness and recognition of the magnitude of mental health problems and the burden on individuals, society and economy. With the extraordinary conditions created by the COVID-19 pandemic, this issue has taken an even more central role in the policy landscape.^20^ COVID-19 is expected to have psychological impacts for health professional, in particular, frontline workers that will be sustained over time.^101–104^

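### Hospitals are randomised within country, but the outcome model names no country-by-time term; no bias is expected, yet precision may be lost

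*Protocol article*

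**What the plan says.** The Data analysis section says that the regression models "will include fixed effects of time, intervention and intervention by time". It then gives the levels: "Hospitals represent higher order units of analysis, and clinicians the lower order unit of analysis". On country it says only "Countries will be treated as fixed effects". An interaction with time is named for the intervention. For country none is named, and none is ruled out. Repeated measures are to be modelled appropriately, but the form is not given, so the article does not say whether a hospital's effect may vary between surveys.

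The Randomisation section says "Within each country, hospitals will be matched on three characteristics", and that random selection is then used to "allocate one hospital within each matched pair of hospitals to the immediate intervention group or the wait list control group".

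The Quantitative data collection section sets surveys in months 11–12, 28–29 and 41–42. The Intervention section equates month 10 with October 2020, so the surveys fall in November–December 2020, April–May 2022 and May–June 2023. Also, "An open cohort design will be employed", so the respondents in a hospital may differ from survey to survey. The Discussion adds that "COVID-19 is expected to have psychological impacts for health professional".

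**The concern.** The intervention effect is read from the intervention-by-time term, which compares changes. A country main effect removes differences in level and does nothing about differences in change. With a single set of time effects, the model assumes that burnout moved in parallel in six countries from late 2020 to mid-2023. The protocol gives no support for that assumption, and it stresses that the health systems differ and that the pandemic affected staff.

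The design randomises within country, so the natural comparison is between arms within country at each wave. If the analysis does not follow the allocation, variation that the design has already removed from the estimate can stay in its standard error. What is at stake is power for the primary outcome.

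**Working it through.** **Protocol inputs (Study sample section).** Prevalence of high emotional exhaustion 30%; target reduction 6 points (to 24%); power 80%; alpha 5%; 200 respondents per hospital; ICC 0.025; 60 hospitals planned in six countries.

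**The protocol's own figure.** With a pooled variance, two-sided, n per arm = [1.96·√(2·0.27·0.73) + 0.8416·√(0.30·0.70 + 0.24·0.76)]² / 0.06² = 858.3. The design effect is 1 + 199·0.025 = 5.975. Then 2·858·5.975 = 10 253, or 51 clusters of 200. The stated size is reproduced, and no figure in the protocol is wrong on this point.

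**Assumptions that the protocol does not give.** Hospital effects correlate 0.8 between surveys; there are 200 different respondents per hospital at each survey; there are 10 hospitals per country; country trends in prevalence have SD 0, 3 or 6 points.

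**Standard error with country-by-time.**
- Individual variance: 0.30·0.70 = 0.21. Between-hospital variance: 0.025·0.21 = 0.00525.
- The part that varies between surveys: 0.2·0.00525 = 0.00105.
- Variance of one hospital's change: 2·0.00105 + 2·0.21/200 = 0.0042.
- SE of the arm difference: √(4·0.0042/60) = 0.0167, or 1.67 points.

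**Standard error without it.** Country trends with variance τ² add, on average, 10·5·τ²/58 to the residual variance of the changes (six countries of 10 hospitals; 60 − 2 = 58 degrees of freedom).
- τ = 3 points: 0.0042 + 50·0.0009/58 = 0.00498; SE = √(4·0.00498/60) = 1.82 points.
- τ = 6 points: 0.0042 + 50·0.0036/58 = 0.00730; SE = √(4·0.00730/60) = 2.21 points.

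**Simulation** of hospital changes with no intervention effect and pair randomisation within country (6000 runs per setting):

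| Trend SD (points) | True SD of estimate | Model SE, term omitted | Type I error, omitted | Model SE, term included |
|---|---|---|---|---|
| 0 | 1.66 | 1.67 | 4.9% | 1.67 |
| 3 | 1.70 | 1.81 | 3.8% | 1.67 |
| 6 | 1.67 | 2.18 | 1.5% | 1.67 |

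The mean estimate is within 0.1 points of zero throughout. Type I error with the term is 4.8% to 5.2%. The true spread of the estimate does not grow with the trends; only the reported standard error does.

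**Uneven countries and hospital sizes** (3 to 20 hospitals per country, size CV about 0.5). The mean estimate is still zero. At trend SD 6 the true SD is 1.84–1.87 without the term and 1.70–1.72 with it, about 8–9% more noise; at trend SD 3 it is about 2%. At trend SD 6 the model SE is 2.10–2.11 without and 1.63–1.64 with the term.

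**Power for 6 points.** Using Φ(6/SE − 1.96):
- SE 1.67: Φ(1.63) = 95%.
- SE 1.81: Φ(1.35) = 91%.
- SE 2.18: Φ(0.79) = 79%.

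This formula takes the inflated SE as the real spread. Keeping the true spread at 1.67, Φ((6 − 1.96·SE)/1.67) gives Φ(1.47) = 93% and Φ(1.03) = 85%. So 91% and 79% are the pessimistic ends of 91–93% and 79–85%. All are on this assumed change-score scale and do not replace the protocol's own calculation.

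**Hospital random intercept only.** Over two surveys, a country's departure from the common trend appears as plus or minus half its size around the hospital's average. It adds τ²/4 to an individual variance of 0.21: 0.000225 (0.1%) at 3 points and 0.0009 (0.4%) at 6 points. The reported SE hardly moves.

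**The case against.** A reader might infer that country-specific pandemic trends will be mistaken for an intervention effect. The documents do not support this. Allocation within matched pairs in each country makes country trends nearly orthogonal to arm, and no systematic shift appears in any setting examined. Only chance imbalance lets them through, and as noise. In a harsher setting (response CV 0.6, 10% of hospitals lost, clinician weighting), the total SD of the estimate rises from 1.91 to 1.98 points at trend SD 3 and from 1.94 to 2.12 at trend SD 5. Those response and loss figures are assumptions too.

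Three further objections carry weight. First, the article does not say that country enters only as a level effect; that is the literal reading of a short paragraph, and a fuller plan may contain the interaction. Second, the loss of precision needs an error term for hospital-level change, which the article does not name. Third, divergent trends are assumed: the Discussion expects the pandemic to affect staff but does not say that countries will differ in this.

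What remains is that the article does list its model terms, names an interaction with time for one factor and not for the other, and so describes an analysis of change that does not follow the groups used for allocation. A plan that adds the term later would improve on the published model.

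**Conclusion.** The point holds as a matter of precision and of matching the analysis to the randomisation. It does not hold as a claim of bias. Under a standard error that properly reflects hospital-level change, omitting country-by-time makes that error about 8% too large at a trend SD of 3 points (1.81 against 1.67) and about 31% too large at 6 points (2.18 against 1.67). The test is then conservative, so a real effect might be missed, but no false claim of benefit follows. At a trend SD of 3 points the harm is modest and power stays well above 80%; at 6 points power comes down to roughly the planned level.

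These sizes rest on the assumed trend SDs, the assumed correlation of 0.8 and near-equal numbers of hospitals per country. If the fitted model has only a hospital random intercept, the inflation does not arise. That does not make such a model sound: its SE under the same assumptions would be about √(4·0.0021/60) = 1.18 points against a true spread of about 1.67, a separate matter that country-by-time does not cure.

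**What to change.** Add country-by-time fixed effects, with time as categorical waves, to every clinician-level outcome model, so that the arms are compared within country at each wave. Pair-by-time would follow the allocation more closely still but uses many more parameters; country-by-time is enough to remove the country trends. State the choice before outcome data are analysed by arm.

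The cost is five extra parameters per follow-up wave, ten over T1 and T2, with no new data. If the trends turn out equal, the loss of precision is negligible: in the zero-trend simulation with 10 hospitals per country the SE was 1.67 points with and without the term.
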